#### The FACAM intervention

The FACAM intervention consists of assigning a specific support person (FACAM person in the following) to each pregnant woman in the intervention group, a person expected to hold this contact until school-age of the child. The intervention is flexible and tailored to each woman’s individual needs. Theoretically, the intervention builds on theories on how to reduce inequality in health and mentalization theory [56, 57] The idea is that if a pregnant woman or mother has access to practical help and support from a professional she trusts, then she can focus more on parenting the child. There is no strict manual for the intervention but guidelines are specifying different tasks that the FACAM person should address with the participant and how often they should be in contact. The tasks include attending with the participant at healthcare and/or social care visits during pregnancy and after birth or participating in consultations with the midwife, general practitioner, social worker, or job consultant. The tasks also include extra home visits or telephone calls to support the family depending on their needs. Focus for contacts can be practical issues such as reminding the family of inoculations, guiding them on how to register the infant for daycare, but also conversations about the economy, family functioning, health, contraception, childhood upbringing, and mother-child attachment for example. The Danish guidelines are available from the corresponding author. An important task for the FACAM person is to guide and refer the family to appropriate support from the hospital, from child care services, or relevant third sector volunteer organizations. During pregnancy and the first year of the child’s life, the FACAM person can offer up to a total of 47 h of support to the family. Depending on the initial level of concern, all FACAM mothers are also offered either a group-based or an individual-based attachment-based course during pregnancy and the first months of the child’s life. Families with a low level of concern are offered eight 2-h sessions of the Circle of Security Parenting Groups Program (COS-P) from when the child is around 2 months old. Families with a medium or high level of concern are offered up to 50 h of individual sessions with a focus on attachment (including an attachment interview and a focus on mentalization). From when the child is 1 year and until it starts school at age 6, the FACAM person can offer up to 10 h of support to the family each year. It is the intention that the FACAM person is consistent over time. For shorter periods of absence, another FAMKO person will take over the contact with the family if necessary. New FAMKO persons will receive thorough training and support from the other FAMKO persons.

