
The FACAM person is either a health visitor or a family therapist employed by Odense Municipality. The FACAM persons have participated in a 4-day mentalization-based training and several 1-day courses with a focus on, for example, mental health issues and third sector organizations. They also receive supervision from a clinical psychologist. Furthermore, all health visitors employed at Odense municipality also receive training in the Alarm Distress Baby Scale (ADBB) method. For families where the professionals have a low level of concern, a health visitor is appointed as the FACAM person. They will also act as a regular health visitor for the family. For families with a medium or high level of concern, the FACAM person will be a family therapist. For these families, the regular health visits in the home will be conducted by a health visitor who may not be trained as a FACAM person.

Participants are allowed to receive any other care during the trial. If a participant does not wish to continue with the FACAM intervention or decides to move from Odense municipality, the intervention will be discontinued.

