When a mother has consented to participate, a research team member registers the participant and sends out the baseline questionnaire. When the participant has filled out the baseline questionnaire, the participant is randomized by a research team member to receive either FACAM or CAU (1:1). The randomization is conducted with the tool “OPEN randomize” in REDCap and the procedure is logged. The randomization sequence was generated by an independent data analyst before recruitment started. Participants are stratified into two groups according to the level of concern assessed by the healthcare professionals which is filled out when participants are invited to participate in the study (levels 1 and 2 are categorized as a high concern, and levels 3 and 4 are categorized as a low concern). When the participant is randomized, the researcher informs the participant and the project coordinator at the municipality about which group the participant is allocated to. The project coordinator at Odense municipality then allocates a FACAM-person to the intervention families prioritizing FAMKO persons with free capacity in the same geographical area. If a group of FAMKO persons with free capacity is under a lot of pressure due to, e.g., sickness, the coordinator will then usually allocate a FAMKO person from another group. After the FAMKO person is allocated, the intervention commences.

The consent form and other related documentation are given to participants are available from the authors on request. The study has no trial steering committee or data monitoring committee as this is not required for behavioral interventions [59, 60].

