#### Fidelity

During the study period, interdisciplinary meetings with the FACAM persons will be held monthly to support uniformity in the care provided to the families. Furthermore, cross-sectorial meetings with participants from the child-and-youth administration, the alcohol and drug treatment, the family clinic, the FACAM persons, the project leaders, and the researchers are held twice a year to support the cross-sectorial collaboration.

We will collect data on the kind of intervention (e.g., method and provider) and the intensity (number and length of sessions) for both intervention and CAU participants. For the intervention group, the FACAM person will answer a short questionnaire after each visit indicating which kind of support they have offered to the family. Participation in the attachment sessions will also be documented.

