### Data analysis

The primary outcome (CIB parental sensitivity at 12 months) is tested using linear regression with robust standard errors since we are interested in the mean difference between the groups but do not expect a perfectly normal distribution of data. The treatment effect is estimated as a fixed effect using a binary indicator of treatment. A Wilcoxon rank-sum test will be used in the case of severe non-normality. Variables with indications (*p* < 0.1) of the differences between intervention and CAU groups at baseline are used as control variables. Missing data is handled using multiple imputations using all available baseline data. Secondary outcomes are analyzed following the same principles.

Additional exploratory analyses will be carried out in a mixed-effects regression framework. This allows for growth curve estimation. Two-sided tests with 0.05 significance levels are applied throughout.

In addition to the primary analysis, we will perform subgroup analyses to examine the potential differences between subsets of participants. Hence, we analyze the subgroups according to the following characteristics: primiparous or multiparous, education (high school or less versus more than high school), concern about the family (level 1/2 or level 3/4), provider (health visitor or family therapist), adult attachment style (ECR-S), initial trauma level (ACE < 3 or ACE ≥ 3), the initial level of reflective function (lowest 50% versus highest 50%), the initial level of depression or anxiety (clinical or not-clinical level), and attendance (dose).

The primary analysis will be based on the intention-to-treat (ITT) principle, aiming to include all participants in the arm they were originally allocated to irrespective of the amount of treatment received. Missing data is handled using multiple imputations using all available baseline data. Sensitivity analyses will be performed to investigate the potential impact of missing data, in particular, by using a pre-specified conservative multiple imputation strategy and a complete case analysis.

We do not expect that participants will be harmed by the study and therefore have no predefined stopping guidelines and no a priori planned interim analyses.

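### Provider and attendance (dose) are listed as subgroups beside baseline factors, but provider repeats the concern-level subgroup and attendance gives no randomised comparison

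*Protocol article*

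**What the plan says.** The Data analysis section gives one list of subgroup characteristics. It runs from parity and education through "concern about the family (level 1/2 or level 3/4), provider (health visitor or family therapist") to adult attachment, trauma and reflective functioning, and closes with "the initial level of depression or anxiety (clinical or not-clinical level), and attendance (dose"). Nothing in the list separates factors fixed before allocation from those that arise after it.

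The section on the FACAM intervention explains what provider means. The intervention consists of "assigning a specific support person (FACAM person in the following) to each pregnant woman in the intervention group". On profession it says: "The FACAM person is either a health visitor or a family therapist employed by Odense Municipality". The choice follows a rule: "For families where the professionals have a low level of concern, a health visitor is appointed as the FACAM person", and "For families with a medium or high level of concern, the FACAM person will be a family therapist".

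Under Procedures and randomization, the municipal coordinator allocates the FACAM person once the arm is known, and only to intervention families. Concern level is rated at the first consultation and is the stratification factor: "levels 1 and 2 are categorized as a high concern, and levels 3 and 4 are categorized as a low concern".

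On dose, the Fidelity section records the kind and intensity of intervention in both arms, plus a FACAM visit questionnaire in the intervention arm. It adds: "Participation in the attachment sessions will also be documented".

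**The concern.** A subgroup analysis of a randomised trial is a set of smaller randomised comparisons, provided that membership is fixed independently of arm. Two of the listed characteristics do not meet that condition as written.

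- **Provider.** The health visitor or family therapist split describes the FACAM person, whom control women do not have. Its value follows from concern level, which is already in the list. A difference between the two provider groups cannot be told apart from a difference between lower-risk and higher-risk families.
- **Attendance.** How much contact a woman has depends on her need, her engagement and what she is offered, all of it after allocation. High attenders have no randomised counterpart in usual care.

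Which profession should give the support, and how much of it, are questions that a service planner would bring to this trial. The Discussion says the results should serve the planning and organisation of care. Results for these two characteristics, printed beside genuine subgroups, could be read as answers when they are not.

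**Working it through.** **Yardstick.** The point rests on no stated figure, but the planned effect of 0.33 SD is used for scale. It reproduces: per group 2 × (1.960 + 0.842)² / 0.33² = 144.2, rounded up to 145, so 290 in total, as stated under Sample size justification.

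**1. Provider against concern level**

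| Concern level at enrolment | Stratum and listed subgroup | FACAM provider by the rule |
|---|---|---|
| 1 (high) | 1/2 | family therapist |
| 2 (medium) | 1/2 | family therapist |
| 3 (low) | 3/4 | health visitor |
| 4 (few or none) | 3/4 | not stated; health visitor assumed |

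This assumes that the rating behind the appointment is the one made at enrolment. Let T = 1 for FACAM, H = 1 for levels 1/2 and P = 1 for a family therapist as FACAM person. The rule makes P = T × H. A model with intercept, T, H, T × H and P then has 5 columns but rank 4, and within FACAM the correlation of P with H is 1.0. No provider effect can be estimated beyond treatment by concern.

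Concern level also sets the attachment course: eight two-hour group sessions for low concern, up to 50 h of individual sessions for medium or high. Provider, family risk and course format move together.

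**2. What a within-FACAM provider contrast would show**

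Take 160 per arm less 15% dropout = 136, and the Discussion's expected two-thirds low concern: about 91 health-visitor and 45 therapist families. In 4,000 simulated trials with no provider effect, the contrast was significant at nominal 5% as follows (the gaps are assumptions):

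| Assumed outcome gap between concern groups | Rejection rate |
|---|---|
| 0.2 SD | 20% |
| 0.3 SD | 37% |
| 0.5 SD | 79% |

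**3. Attendance**

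The documents themselves tie dose to family risk. Support is tailored to need. The maximum offered up to 12 months is 47 + 8 × 2 = 63 h for low concern and 47 + 50 = 97 h for medium or high. Retention is higher in low-concern mothers.

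For the size, suppose FACAM has no effect and attendance and prognosis are bivariate normal with correlation r. The mean of a standard normal above its median is √(2/π) = 0.798. So:

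- above-median attenders minus all controls = 0.798 r
- above-median minus below-median attenders within FACAM = 2 × 0.798 r = 1.596 r

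| r (assumed) | High attenders vs all controls | Rejection rate | High vs low within FACAM | Rejection rate |
|---|---|---|---|---|
| 0.1 | 0.08 SD | 9% | 0.16 SD | 16% |
| 0.2 | 0.16 SD | 18% | 0.32 SD | 46% |
| 0.3 | 0.24 SD | 37% | 0.48 SD | 81% |
| 0.5 | 0.40 SD | 79% | 0.80 SD | over 99% |

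Rejection rates come from 4,000 simulated trials with 136 per arm; with r = 0 both contrasts reject in about 5%. The sign of r could go either way, because greater need can raise contact while lower engagement reduces it.

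**The case against.** **Both variables are recorded in usual care too.** A reader might infer that provider and dose exist only in the FACAM arm. The documents do not support that. The Fidelity section collects provider and intensity for both arms, and usual care includes health-visitor home visits and, where needed, a therapist at the family clinic. What exists in one arm only is the FACAM person and the FACAM dose. The control data describe a different exposure and are also post-randomisation, so they do not supply the missing comparison.

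**A valid provider comparison exists.** This stands. If control women are classed by the provider that their concern level implies, each class is a randomised comparison. The fault is then redundancy, since it is the concern subgroup under another name. For the same reason a reader should not infer that the therapist group must show a worse treatment effect because it holds the high-concern families. Against controls of the same concern level that does not follow; it applies to contrasts within FACAM or against the whole control arm.

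**The article does not say which contrast will be run.** True, and an analysis plan may define dose and the model. The article does not say that attenders will be set against all controls. What it does fix is that both variables stand as subgroups on the same footing as baseline factors.

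**These analyses are secondary.** Also true. They are two of nine characteristics, additional to a primary analysis that includes everyone as randomised.

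**Conclusion.** The point holds for how these two characteristics are classified. Under the article's own rule, provider adds nothing to the level 1/2 versus 3/4 subgroup and cannot separate a provider effect from family risk. This is exact for levels 1 to 3 and inferred for level 4. Attendance is a post-randomisation variable and gives no randomised dose comparison, whichever contrast is chosen.

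The size of any spurious dose result depends on assumed correlations. At 0.2 to 0.3 the false difference is about half to three-quarters of the planned 0.33 when attenders are set against all controls (0.16/0.33 = 0.48; 0.24/0.33 = 0.73). Only the within-FACAM contrast, at 0.32 to 0.48 SD, is about as large as the planned effect or larger; that range should not be read as a bias against controls. The sample size and the primary analysis are untouched.

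**What to change.** - Delete provider from the subgroup list, or state that it is the concern-level subgroup with controls classed by the same rule. Say which provider level 4 families receive, so that the overlap is explicit.
- Move attendance (dose) out of the subgroup list. Report it as a descriptive, non-randomised association within FACAM. Optionally add an exploratory complier-average causal effect (CACE) analysis with randomised arm as the instrument, a contact threshold set in advance and the exclusion restriction stated. That restriction is demanding here, because support is flexible and contact below a threshold may still have an effect. The CACE also answers a different question from dose-response.
- Test the remaining subgroups by treatment-by-subgroup interaction. Note that ACE and prenatal reflective functioning are measured at T1 (gestational week 25), not T0, so the plan should say whether they precede allocation.

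The cost is a change of wording and, if wanted, one extra exploratory analysis that carries the CACE assumption. The contact data are already to be collected.

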#### Baseline measures

In addition to the socio-demographic measures, we include the following measures at baseline to assess the initial level and to account for them as possible moderators or confounders in the effect analyses.

Prenatal Parental Reflective Functioning Questionnaire (P-PRFQ) [61] is a 14-item measure of parental reflective functioning of the pregnant woman’s ability to mentalize. The P-PRFQ is an adaption of the PRFQ [62] and consists of three subscales: opacity of mental states (4 items), reflecting on the fetus-baby (3 items), and dynamic of mental states (5 items). Cronbach’s alpha is 0.77 for the total score and 0.69–0.77 for the three subscales. Responses are on a Likert scale ranging from 1 to 7 with three different scalings: (1) high-low where 7 = optimal PRF and 1 = low PRF, (2) low-high where 1 = optimal PRF and 7 = low PRF, and (3) middle where 4 = optimal PRF and 1 and 7 = low PRF. Scores are summed to a total score ranging from 7 to 98.

Hospital Anxiety and Depression Scale (HADS) [63, 64] is a 14 item measure of anxiety and depression. HADS consist of the two subscales “anxiety” and “depression.” The two subscale scores are summed and range from 0 to 21, where low scores indicate less anxiety and depression.

Experiences in the Close Relationship Scale-Short Form (ECR-S) [65] is a 12-item measure of adult attachment consisting of the two subscales “anxiety” (fear of abandonment and a craving for interpersonal closeness) and “avoidance” (fear of intimacy and interpersonal dependency). Each subscale is scored by summing the items and ranges from 1 to 42, where low scores indicate better attachment.

Adverse Childhood Experience (ACE) Questionnaire is a 10-item measure developed for the ACE study to identify childhood experiences of abuse and neglect. Reponses are yes or no. The total score is summed, and the total range is 0–10 where 0 indicates no experience with childhood abuse and neglect.

PTSD-8 [66] is an 8-item measure of posttraumatic stress disorder (PTSD) symptoms, including intrusion, avoidance, and hypervigilance. The total score is the sum of the items and the range is 8–32, where a low score indicates less PTSD.

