### Sample size justification

Power analysis (based on an extension of the dependent *t*-test) was carried out in the design phase to assess the statistical power for testing the primary outcome. The power calculation is based on a meta-analysis of interventions aimed to improve parenting sensitivity [87]. The overall average effect size was 0.44 (standardized mean difference (SMD)), but for randomized trials, the average effect size was 0.33. For normally distributed outcomes and using a two-sided alpha of 0.05, and a power of 80%, we would need 160 participants to detect an effect size of 0.44 and 290 participants to detect an effect size of 0.33. We expect around 15% dropout and therefore aim to recruit 330 participants.

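### Baseline reflective function and childhood trauma are cut into two groups for the subgroup analyses, which loses precision that the collected scores would keep

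*Protocol article*

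**What the plan says.** In the protocol article, Data analysis says that, beyond the primary analysis, "we will perform subgroup analyses to examine the potential differences between subsets of participants". The list of characteristics includes "the initial level of reflective function (lowest 50% versus highest 50" per cent) and "initial trauma level (ACE < 3 or ACE ≥ 3"). It also splits baseline depression or anxiety at a clinical level, and names adult attachment style (ECR-S) without giving any cut.

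Baseline measures describes the underlying scales as graded. For P-PRFQ: "Scores are summed to a total score ranging from 7 to 98". For ACE: "The total score is summed, and the total range is 0–10". HADS has two summed subscales, each running from 0 to 21. The same section says the baseline measures are collected "to account for them as possible moderators or confounders in the effect analyses".

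Sample size justification covers only the overall comparison on the primary outcome. The article gives no power for any subgroup or interaction analysis and does not plan to use P-PRFQ or ACE as continuous moderators.

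**The concern.** The question behind these analyses is whether the effect of FACAM depends on where the mother starts. Cutting a graded score in two treats women just either side of the cut as opposites and women far apart on the same side as identical. That discards information the trial has already paid to collect, in an analysis the sample size was never meant to support.

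The median split has a second weakness: the boundary is whatever the recruited sample makes it. It is unknown until the data are in and need not mean the same thing in another study. This does not apply to ACE, whose cut at 3 is fixed in advance.

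At stake is the precision and transportability of secondary findings about who benefits. The primary result is not at stake.

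**Working it through.** **Inputs from the protocol article.** The design is "using a two-sided alpha of 0.05, and a power of 80" per cent (Sample size justification), with 1:1 allocation. The planning effect is SMD 0.33: "for randomized trials, the average effect size was 0.33". Dropout is 15%. The recruitment target is 330 in Sample size justification and 320 in Procedures and randomization.

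**Assumptions not in the article.** Outcome SD is 1, the moderator is roughly normal, and the treatment effect is linear in the moderator. Alternatives are shown below.

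**1. The plan's own figure.** Per arm, n = 2(1.96 + 0.8416)² / d².
- d = 0.33: 2 × 7.849 / 0.1089 = 144.2, so 145 per arm and 290 in total. This matches the stated 290.
- d = 0.44: 2 × 7.849 / 0.1936 = 81.1, so 82 per arm and 164 in total, against the stated 160.

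After dropout, 330 × 0.85 is about 280 analysed, and 320 × 0.85 = 272.

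**2. Information kept by a cut.** If a normal score is cut so that a proportion p lies on one side, the share kept is φ(z_p)² / [p(1 − p)]. At the median this is 0.3989² / 0.25 = 2/π = 0.637, a loss of 36.3%. On this question 280 women act like 280 × 0.637 ≈ 178.

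**3. Other score shapes.** The share kept is the squared correlation between the score and its split.

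| Score and cut | Share kept | Loss |
|---|---|---|
| Uniform, median | 0.75 | 25% |
| Normal, median | 0.64 | 36% |
| Exponential, median | 0.48 | 52% |
| ACE-type count, mean 2, cut at 3 | 0.67 | 33% |
| ACE-type count, mean 3, cut at 3 | 0.63 | 37% |
| ACE-type count, mean 4, cut at 3 | 0.56 | 44% |

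The three count rows assume negative binomial distributions capped at 10, with 31%, 48% and 63% of women at 3 or above. The article gives no ACE distribution.

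**4. Power to detect moderation, N = 280.**
- Median split: the SE of the difference between the two subgroup effects is 4/√280 = 0.239. For a difference of 0.33 SMD, Φ(0.33/0.239 − 1.96) = 28%.
- Continuous score: under linearity the same difference corresponds to a slope of 0.33 / (2√(2/π)) = 0.207 per SD, with SE 2/√280 = 0.1195. Φ(0.207/0.1195 − 1.96) = 41%.
- For a difference of 0.66 SMD, the figures are 79% and 93%.
- At N = 272 and N = 290, the 0.33 figures are 27% against 40%, and 29% against 42%.

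For 80% power the split needs a between-half difference of 2.80 × 0.239 ≈ 0.67 SMD. The continuous analysis needs a slope of 2.80 × 0.1195 = 0.335 per SD, which is a between-half difference of 0.335 × 1.596 ≈ 0.53 SMD.

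**5. Simulation check.** With N = 280, 4,000 runs, a normal moderator and a slope of 0.3 per SD, power was 71% for the continuous score and 52% for the median split. The implied share of information kept was 0.62, close to 0.637.

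**6. If each half is only analysed on its own.** With 70 women per arm, power for SMD 0.33 within one half is about 50%.

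**The case against.** The strongest reply is that nothing here is false or contradictory. The cuts are named in advance for analyses that are additional to the primary one, and a pre-stated cut removes the freedom to choose one after seeing results. That stands, and it is why the point is minor. It does not make the cut an efficient choice.

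The article also names no interaction test. That is correct: reading these as moderation analyses rests on combining the stated role of the baseline measures with the stated aim of the subgroup list. If the halves are only analysed separately, step 6 applies and precision is still poor.

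Several stronger readings are tempting but unsupported:
- A reader might take 36% as the loss whatever the data look like. It depends on a roughly normal score and linear moderation, and the article states neither.
- A reader might infer that the continuous score rescues the analysis. It reaches 80% power only for strong moderation. At a slope of 0.335 per SD around a mean effect of 0.33, women one SD below average would gain almost nothing and women one SD above about 0.67.
- The Discussion reports more low-concern women than planned, and a reader might conclude that the P-PRFQ median has moved. The article does not relate P-PRFQ to concern level.
- ECR-S might be thought to be dichotomised too. No cut is stated for it, so it is not part of this point.

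**Conclusion.** The point holds as a low-cost improvement to secondary analyses. The article commits to a sample-median split of P-PRFQ and a cut of ACE at 3, although both are available as graded scores. The cost is about 36% of the information for P-PRFQ under normality and linear moderation (25% to 52% across the other shapes tried), and about 33% to 44% for ACE under assumed distributions. At about 280 analysed, power for a 0.33 SMD difference is 28% with the split and 41% without it, so the analysis remains underpowered for moderation of that size either way.

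One prior question limits the point. Data collection places P-PRFQ and ACE at T1, gestational week 25, while Procedures and randomization has women randomised once the baseline questionnaire is complete. If that means T0, both scores may be measured after allocation, and modelling them continuously does not cure that. HADS is collected at T0 and does not share the problem.

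**What to change.** For whichever scores are kept as moderators, state that moderation is assessed by a treatment × continuous score term in the robust-SE linear regression already planned, for P-PRFQ and ACE and likewise for the HADS subscale scores. Check linearity with a quadratic or spline term. Keep the median split, the ACE cut at 3 and the clinical HADS grouping only to display estimated effects, and report the observed P-PRFQ median. Describe the results as exploratory, since power stays low.

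Settle first whether P-PRFQ and ACE are measured before or after randomisation, and retain them as moderators only if that is resolved.

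The cost is a line or two of analysis wording, with no new data and no loss of the planned presentation. The downside is the linearity assumption, which the added term checks.
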